### **List of Abbreviations**

| **Abbreviation** | **Description** |
| --- | --- |
| AF | Atrial fibrillation (心房細動) |
| BNP | Brain natriuretic peptide (脳性ナトリウム利尿ペプチド) |
| CIED | Cardiovascular implantable electronic device (植込み型心臓デバイス) |
| CRB | Certified Review Board (臨床研究審査委員会) |
| CRF | Case Report Form (症例報告書) |
| CTCAE | Common Terminology Criteria for Adverse Events (有害事象 共通用語規準) |
| EDC | Electronic Data Capture (電子的臨床検査情報収集) |
| FAS | Full analysis set (最大の解析対象集団) |
| GCP | Good Clinical Practice (医薬品の臨床試験の実施の基準に関する省令) |
| HFrEF | Heart failure with reduced ejection fraction (左室駆出率の低下した心不全) |
| ICD | Implantable cardioverter defibrillator (植込み型除細動器) |
| ILR | Implantable loop recorder (植込み型ループレコーダー) |
| IVS | Interventricular septum thickness (心室中隔厚) |
| jRCT | Japan Registry of Clinical Trials (臨床研究等提出・公開システム) |
| LAD | Left atrial diameter (左房径) |
| LVDd | Left ventricular end-diastolic diameter (左室拡張末期径) |
| LVDs | Left ventricular end-systolic diameter (左室収縮末期径) |
| LVEF | Left ventricular ejection fraction (左室駆出率) |
| LVPW | Left ventricle posterior wall thickness (左室後壁厚) |
| PMDA | Pharmaceuticals and Medical Devices Agency (医薬品医療機器総合機構) |
| PPS | Per protocol set (研究計画書に適合した対象集団) |
| SAS | Safety Analysis Set (安全性解析対象集団) |
| SGLT | Sodium glucose co-transporter (ナトリウム－グルコース共輸送体) |
| TIA | Transient ischemic attack (一過性脳虚血発作) |

**Purpose of the Study**
To investigate the clinical utility of continuous heart rhythm monitoring using an implantable loop recorder (ILR) in detecting asymptomatic arrhythmias in patients with heart failure with reduced ejection fraction (HFrEF)—patients who have not been diagnosed with atrial fibrillation (AF).

**Research Design**
Single-center, open-label, non-controlled study

**Nature of the Study**
Exploratory research

**Investigational Medical Devices**

- **General name**: Implantable data recorder for electrocardiograms
  **Product name**: Medtronic LINQ II
  **Classification**: Highly controlled medical device (Class IV)
  **Manufacturer/Distributor**: Medtronic Japan

Note: Includes “MyCareLink Relay Home Communicator” as a component.

- **General name**: Program for management of implantable active devices
  **Product name**: Medtronic Reveal LINQ Mobile Manager
  **Classification**: Highly controlled medical device (Class III)
  **Manufacturer/Distributor**: Medtronic Japan
- **General name**: Programmer for implantable active devices
  **Product name**: Medtronic 24967 Patient Connector
  **Classification**: Highly controlled medical device (Class III)
  **Manufacturer/Distributor**: Medtronic Japan

**Subjects**
Patients with HFrEF who have not been diagnosed with AF

**Inclusion Criteria**
All of the following conditions must be met:

1. Patients with HFrEF (left ventricular ejection fraction ≤ 40%)
2. Patients who are undergoing appropriate pharmacotherapy for HFrEF and are currently in outpatient care or are able to attend outpatient care
3. Patients with a CHADS2 score ≥ 1
4. Age ≥ 20 at the time of consent
5. Patients who provide written informed consent

**Exclusion Criteria**
Any of the following:

1. Patients who already have an implanted cardiovascular electronic device (CIED) capable of detecting supraventricular arrhythmias (i.e., a permanent pacemaker, ICD, or ILR)
2. Patients diagnosed with AF at the time of consent
3. Patients whose life expectancy is considered to be within 1 year
4. Patients in an immunocompromised state
5. Patients with an active infection
6. Patients whose subcutaneous tissue is too thin at the implantation site, making safe ILR implantation difficult
7. Any patient deemed inappropriate for this study by the principal or sub-investigator

**Endpoints**

- **Primary Endpoint**
  Proportion of patients in whom AF or non-sustained or sustained ventricular tachycardia is detected

Defined as the proportion of patients (in the analysis population) who exhibit the following on ILR:

- - AF of ≥6 minutes duration
  - Non-sustained VT: rate >150 bpm, ≥16 consecutive beats, ≤30 seconds
  - Sustained VT: rate >150 bpm, ≥30 seconds
- **Secondary Endpoints**
  - Proportion of patients with pauses ≥4.5 seconds
  - Proportion of patients with bradycardia <30 bpm
  - Proportion of patients with high-grade AV block
  - Proportion of patients who received a permanent pacemaker, ICD, catheter ablation, or antiarrhythmic drug therapy
  - All-cause mortality rate
  - Cardiovascular mortality rate
  - Proportion of patients requiring hospitalization due to cardiovascular disease or heart failure
  - Proportion of patients who experienced stroke
- **Safety Endpoints**
  - Incidence of adverse events related to ILR implantation
  - Incidence of device malfunctions

**Protocol Treatment**
After obtaining written informed consent, the ILR will be implanted subcutaneously in the left anterior chest area under local anesthesia by the principal or sub-investigator. Post-implantation, remote monitoring (using Medtronic CareLink) will be performed every 6 months to assess the arrhythmic events specified in Section 5.1.

For the primary endpoint and secondary endpoints 1–3, if an arrhythmic event is detected via remote monitoring, an alert email will be sent or forwarded to an evaluation physician who is separate from the outpatient attending physician. The evaluation physician will review the ECG stored on the server and make a diagnosis (determine whether an arrhythmic event occurred). If the physician judges that immediate communication with the outpatient physician is medically necessary, the monitoring results will be reported to the outpatient physician as needed. If the patient experiences symptoms suggestive of arrhythmia, the ILR data may be checked at any time.

Patients will continue outpatient visits every 1–3 months, as before ILR implantation. During these visits, the presence or absence of events related to secondary endpoints 4–8 will be verified, along with other clinical progress.

**Target Sample Size**
35 subjects

**Study Period**
Overall study period: From the date of jRCT publication of the implementation plan to September 30, 2030 (6 years)

- Planned enrollment period: 2 years
- Observation period: 3 years after enrollment ends
- Analysis period: 1 year

**Number of Study Sites**
Single-center (Tokyo Medical and Dental University Hospital)

### **3. Background of the Clinical Research**

In Japan’s statistics of causes of death, heart disease ranks second; among these, heart failure accounts for the largest proportion. With an aging society, the number of heart failure patients continues to increase, projected to reach 1.2 million by 2020. About half of these patients have reduced left ventricular ejection fraction, and the 2017 revised “Guidelines for Diagnosis and Treatment of Acute and Chronic Heart Failure” define HFrEF (Heart Failure with reduced Ejection Fraction) as an LVEF <40%.

Atrial fibrillation (AF) is the most frequently coexisting arrhythmia in heart failure, and its prevalence increases in more severe heart failure cases, serving as a trigger for both exacerbation of heart failure and thromboembolism. If detected at an early stage, ablation or antiarrhythmic drug therapy can be used for rhythm control; in chronic cases, the arrhythmia may be managed by rate control with medication. Ventricular arrhythmias are also common in HFrEF and can lead to sudden cardiac death. High-risk cases may require antiarrhythmic drug therapy or implantation of an implantable cardioverter defibrillator (ICD).

Since arrhythmias typically occur intermittently and often without symptoms, diagnosing them in regular outpatient care can be difficult. It is known that the diagnostic accuracy for arrhythmias depends on the length of time ECG is evaluated (monitoring period), and implantable loop recorders (ILRs)—implanted subcutaneously in the left anterior chest—allow continuous ECG monitoring and thus provide the highest accuracy. The “Medtronic LINQ II” device we will use in this study is small and light (45 × 8 × 4.2 mm, 4 g), and its monitoring data can be checked by healthcare providers at any time via a remote monitoring system. While it is an already-approved device in Japan, domestic approval is limited to (1) patients with unexplained syncope and (2) patients with unexplained cerebral infarction. By contrast, it has broader indications in the U.S. and Europe, including use for AF monitoring. For instance, a large clinical trial by Sanna et al., involving 441 patients with cryptogenic stroke in whom AF was not detected by conventional means, randomized them into ILR implantation vs. conventional monitoring groups for 6 months, demonstrating a significantly higher detection rate of AF in the ILR group (8.9% vs. 1.4%).

For HFrEF patients (who are at high risk of developing AF and other arrhythmias), continuous ECG monitoring by ILR may facilitate the earlier detection of arrhythmias and earlier therapeutic intervention, potentially improving mortality.

Since there are no published data on ILR-based continuous ECG monitoring in the target population of this study (patients with HFrEF), the exact incidence of newly identified arrhythmias remains unclear. This study is exploratory, enrolling up to 35 patients who are likely eligible for ILR implantation over 2 years, to examine the exploratory utility of ILR for HFrEF. Patients may benefit from earlier detection and intervention for arrhythmias. Potential disadvantages include skin-related complications (infection, erosion, bleeding, etc.) at the implantation site. Early overseas reports in patients receiving ILRs for unexplained syncope, unexplained stroke, or AF monitoring indicated a complication rate of about 1.5%, with about half resolving conservatively and the other half requiring device explant. We will follow subjects for one year (the main analysis time point) and continue observation for up to three years, matching the battery life of the device. Should promising results be obtained, we will consider, in collaboration with the manufacturer, the possibility of conducting a subsequent clinical trial aimed at expanding indications to use ILRs for HF patients.

1. Okura Y, et al. Impending epidemic: future projection of heart failure in Japan to the year 2055. Circ J 2008; 72: 489-491.
2. Guidelines for Diagnosis and Treatment of Acute and Chronic Heart Failure （JCS 2017/JHFS 2017）
3. JCS/JHRS 2019 Guideline on Non-Pharmacotherapy of Cardiac Arrhythmias
4. Aguilar M, et al. Influence of Monitoring Strategy on Assessment of Ablation Success and Postablation Atrial Fibrillation Burden Assessment: Implications for Practice and Clinical Trial Design. Circulation. 2022;145:21-30.
5. Sanna T, et al. Cryptogenic stroke and underlying atrial fibrillation. N Engl J Med. 2014;370:2478-86.
6. Mittal S, et al. Safety Profile of a Miniaturized Insertable Cardiac Monitor: Results from Two Prospective Trials. Pacing Clin Electrophysiol. 2015;38:1464-9.

### **4. Purpose of the Clinical Research**

To investigate the clinical utility of continuous heart rhythm monitoring using ILRs in detecting asymptomatic arrhythmias among HFrEF patients not diagnosed with AF.

### **5. Details of the Clinical Research**

#### 5.1 Primary and Secondary Endpoints

#### (See “8. Evaluation of Efficacy” for details.) The primary analysis will use data at 1 year post-implantation; after all patients have completed the 3-year follow-up, a final analysis will be performed.

- **Primary Endpoint**
  Proportion of patients in whom AF or non-sustained or sustained VT is detected

Definition: Among the analysis population, the percentage of patients with any of:

- - AF lasting ≥6 minutes
  - Non-sustained VT: heart rate >150 bpm, ≥16 consecutive beats, ≤30 s
  - Sustained VT: heart rate >150 bpm, lasting ≥30 s

Rationale: These arrhythmias would clinically warrant consideration of intervention (pharmacological, ablation, or device-based).

- **Secondary Endpoints**
  - Proportion of patients with pauses ≥4.5 seconds
  - Proportion of patients with bradycardia <30 bpm
  - Proportion of patients with high-grade AV block
  - Proportion of patients receiving permanent pacemakers, ICDs, catheter ablation, or antiarrhythmic drug therapy
  - All-cause mortality
  - Cardiovascular mortality
  - Proportion of patients requiring hospitalization for cardiovascular disease or heart failure
  - Proportion of patients experiencing stroke

Rationale:

- - (1)–(3): They may require consideration of therapeutic intervention.
  - (4): To evaluate the effect of continuous ECG monitoring by ILR on treatment decisions.
  - (5)–(8): To evaluate the relationship between ILR findings and clinical outcomes.
- **Safety Evaluation Items**
  - Incidence of adverse events related to ILR implantation
  - Incidence of malfunctions

(Rationale: General safety assessment items.)

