##### 7.1.3 Remote Monitoring

- The CareLink system (Medtronic) transmits data from a home-based communicator (“MyCareLink Relay”) to a dedicated server. Physicians can access the data at any time.
- Every 6 months for 3 years, a separate “evaluation physician” (not the outpatient physician) checks the arrhythmia event data from the ILR. The results are recorded in the CRF.
- If the ILR records an arrhythmia event, an alert email is sent to the evaluation physician, who then reviews the ECG on the server to confirm. If urgent, the evaluation physician notifies the outpatient physician immediately. If the patient reports symptoms, the ILR data can be reviewed at any time.

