##### 7.2.2 Observation/Examination Items

1. **Informed Consent**
   Date of written informed consent
2. **Subject Background**
   - **Basic info**: DOB, age, sex, height, weight, BMI
   - **Comorbidities**: HF, hypertension, diabetes, stroke/TIA (for CHADS2), vascular disease (for CHA2DS2-VASc)
   - **Dialysis**: presence or absence
   - **Past cardiac surgery**: type, date
   - **Hospitalization history for HF**: presence, number of admissions, most recent admission date
   - **Current medications**: antiplatelet/anticoagulants, diuretics, beta-blockers, RAA inhibitors, MRAs, SGLT2 inhibitors, other HF therapies, antiarrhythmics
3. **Pre-implantation (Registration) Tests**
   - **Echocardiogram**: LAD, LVDd, LVDs, LVEF, IVS, LVPW, etc.
   - **Blood test**: BNP
   - **ECG**: 12-lead ECG to confirm rhythm (sinus, AF/flutter, paced, etc.)
   - **Chest X-ray**: cardio-thoracic ratio (CTR)
4. **At Implantation**
   - **ECG**: Monitor ECG (or 12-lead if possible) to confirm rhythm
5. **ILR Remote Monitoring**
   - Date of evaluation, evaluator
   - **AF ≥6 minutes**: presence/absence, date/time, number of events, total duration, etc.
   - **Non-sustained VT** (HR >150, ≥16 beats, ≤30 s)
   - **Sustained VT** (HR >150, ≥30 s)
   - **Pauses ≥4.5 s**
   - **Bradycardia <30 bpm**
   - **High-grade AV block**
6. **Clinical Course**
   - Mortality (date, CV or non-CV, details)
   - CV or HF hospitalizations (date, details)
   - Stroke (date, details)
   - Implantation of a permanent pacemaker, ICD therapy, catheter ablation, AAD therapy (dates, details)
7. **Adverse Events**
   - Onset date, resolution date, severity (Grade), treatment, outcome, seriousness, relationship to ILR, whether ILR explanted, etc.
8. **Device Malfunctions**
   - Malfunction name, onset/end date, presence of adverse event, whether ILR explanted, etc.

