##### 8.1.2 Secondary Endpoints

1. Proportion of patients with pauses ≥4.5 s
2. Proportion of patients with bradycardia <30 bpm
3. Proportion of patients with high-grade AV block
4. Proportion of patients receiving pacemaker, ICD, ablation, or antiarrhythmic therapy
5. All-cause mortality
6. Cardiovascular mortality
7. Proportion with hospitalizations for CV disease/HF
8. Proportion who experienced stroke

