### 13.3 Handling of Genetic or Incidental Findings Related to Study Participants

This study does not involve any tests or analyses that would yield critical information about the participants’ health or genetic characteristics.

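### Secondary endpoint 4 is meant to show the ILR's effect on treatment decisions, but nothing ties a counted therapy to an ILR finding, and anticoagulant starts are not collected

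*Protocol*

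**What the plan says.** Section 5.1 defines endpoint 4 as "Proportion of patients receiving permanent pacemakers, ICDs, catheter ablation, or antiarrhythmic drug therapy". Section 8.1.2 shortens this to "Proportion of patients receiving pacemaker, ICD, ablation, or antiarrhythmic therapy", and the Overview lists the same four therapies in the past tense. The rationale in Section 5.1 is "To evaluate the effect of continuous ECG monitoring by ILR on treatment decisions". Section 5.2.1 states a single-arm design without control.

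Section 7.2.2 has two relevant lists. Baseline medication covers "antiplatelet/anticoagulants, diuretics, beta-blockers, RAA inhibitors, MRAs, SGLT2 inhibitors, other HF therapies, antiarrhythmics". Under clinical course, the follow-up items include "Implantation of a permanent pacemaker, ICD therapy, catheter ablation, AAD therapy (dates, details". Anticoagulants appear only in the baseline list.

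On the route from finding to treating physician, the Overview and Section 7.1.3 send alerts to an evaluation physician who is not the outpatient physician. Section 7.1.3 adds "If urgent, the evaluation physician notifies the outpatient physician immediately". The six-monthly results are entered in the CRF. Sections 5.4 and 7.1.3 also leave the recordings open to medical staff or physicians at any time.

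Section 7.3.2 lists pacemaker and ICD implantation as prohibited, and Section 7.6 makes prohibited therapy a reason for discontinuing the subject.

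**The concern.** Without a comparator, a change in treatment can be credited to the ILR only if the data show that an ILR finding led to it. The endpoint as worded asks only whether a therapy was given. Section 3 itself expects some high-risk patients with HFrEF to need an antiarrhythmic drug or an ICD, so therapy unrelated to the ILR is foreseeable in this population.

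The endpoint also misses one treatment decision that can follow AF detection. Section 3 links AF to thromboembolism, entry requires a CHADS2 score of at least 1, and stroke is a secondary endpoint. Yet a newly started anticoagulant is neither counted nor listed for collection.

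This is the only endpoint whose stated rationale is the effect on treatment, and Section 3 says promising results may lead to a trial aimed at wider indications. A proportion that cannot be attributed to the device would be weak support for that step. Attribution that was not recorded at the time may not be recoverable at analysis.

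**Working it through.** The protocol states no expected rate, precision or test for endpoint 4, so there is no figure to reproduce. The check sets the purpose against what the data can identify, and then illustrates the mixing.

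**Step 1: purpose against definition.**

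| What the rationale needs | What the protocol provides |
|---|---|
| Therapy started after implantation | No such condition in the Overview, 5.1 or 8.1.2; dates collected in 7.2.2 |
| Therapy prompted by an ILR finding | No condition, and no item for the trigger in 7.2.2 |
| A comparator, if attribution is not recorded | None (5.2.1) |
| The treatment decisions that can follow AF detection | Ablation, antiarrhythmic drugs and devices; anticoagulant starts absent |

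**Step 2: what an observed count identifies.** Each patient contributes 1/35 = 2.9 percentage points. Suppose 7 patients are counted, 7/35 = 20.0% (exact 95% CI 8.4% to 36.9%). Without an attribution item, the number prompted by the ILR lies anywhere between two limits:

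- all 7: 7/35 = 20.0% (8.4% to 36.9%)
- none: 0/35 = 0% (0% to 10.0%)

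Recorded dates can narrow this range by ruling out therapy that preceded every finding. They cannot show that a later therapy was given because of a finding. Section 7.2.2 spells out date and time of episodes for AF only.

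**Step 3: illustration of the mixing.** Take t as the share with ILR-prompted therapy and u as the share with new therapy unrelated to the ILR, assumed independent, with therapy before implantation left out. Then

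counted proportion = 1 − (1 − u)(1 − t), and prompted share of those counted = t / counted proportion.

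Both rates are assumptions; the documents give neither. With t = 10%:

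| u | Counted proportion | Expected patients of 35 | Prompted share |
|---|---|---|---|
| 0% | 10% | 3.5 | 100% |
| 10% | 1 − 0.9 × 0.9 = 19% | 6.65 | 53% |
| 20% | 1 − 0.8 × 0.9 = 28% | 9.8 | 36% |

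The same ILR effect gives a reading from 10% to 28%.

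**Step 4: anticoagulation.** A patient whose only change after detected AF is a new anticoagulant adds 0 to endpoint 4 under every definition in the protocol.

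**Step 5: device components.** Pacemaker and ICD are two of the four components (5.1). They are also prohibited therapies (7.3.2), and a prohibited therapy discontinues the subject (7.6). Section 7.1.5 ends observation when a new device makes the ILR redundant. The text does not say how such an implantation is to be counted.

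**The case against.** The best defence is that endpoint 4 is one of eight secondary endpoints in a study declared exploratory and uncontrolled, that the study's stated purpose is detection (which the primary endpoint addresses), and that a counting rule for new therapy could sit in a SAP that is not shown. The first two points limit the weight of the concern. The third covers new onset, because dates are collected. It does not cover attribution or anticoagulant starts, which need data that the protocol does not list.

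Leaving out anticoagulation can also be defended as a choice: the endpoint matches the kinds of intervention named in Section 5.1, and stroke is captured separately. No passage promises that anticoagulation will be counted. The point that stands is narrower: a rationale about treatment decisions is served incompletely while these starts go unrecorded.

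Four stronger readings are tempting, and the documents do not support them.

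- *Antiarrhythmics taken before implantation inflate the endpoint from the outset.* The wording fails to exclude them, but Sections 7.1.4 and 7.2.2 point the other way: endpoint 4 is checked as events at follow-up visits, and baseline drugs are listed apart from dated follow-up therapies. Existing pacemakers and ICDs are excluded at entry. No rate of baseline use is given, so no floor can be calculated.
- *Only urgent findings reach the treating physician.* Only active notification is limited in this way; the data can be viewed at any time.
- *Findings that are not passed on bias the endpoint downwards.* A finding that never reaches the treating physician changes no decision, so a low proportion would correctly describe monitoring as run here.
- *Section 13.3 contradicts the endpoint.* Its sentence "This study does not involve any tests or analyses that would yield critical information" stands under a heading on genetic and incidental findings, whereas arrhythmias on the ILR are the study's target.

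**Conclusion.** The point holds in limited form. Following the protocol exactly yields a proportion that cannot answer the question Section 5.1 sets for endpoint 4, because ILR-prompted and unrelated therapy are counted together and no item separates them. The omission of anticoagulant starts adds a gap in the same endpoint. This should be changed, but it does not touch the primary endpoint.

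The size cannot be determined from the documents. For any observed count, the ILR-prompted part is bounded only by zero and the full count, before any narrowing by dates. The 10% to 28% range rests on the assumed rates and on independence, and only illustrates the mixing.

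Two textual matters belong with it. Section 5.1 says of all primary-endpoint arrhythmias "These arrhythmias would clinically warrant consideration of intervention", while the Overview and Section 7.1.3 describe active reporting only when it is urgent; how non-urgent findings are passed on is not stated. And device implantation is both a component of the endpoint and a prohibited therapy. Both sets of passages must be reconciled. Which clinical rule should apply is for the investigators.

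**What to change.** 1. In the Overview, 5.1 and 8.1.2, define endpoint 4 as any of the listed therapies newly started after ILR implantation.
2. Add to the clinical-course items in 7.2.2 a yes/no for whether an ILR finding prompted the therapy, with the date of the triggering episode. Report ILR-prompted and other new therapy separately.
3. Add new anticoagulant starts to the follow-up items and report them as a separate line.
4. Record for each confirmed event whether and when it was reported to the outpatient physician. Use this as description only; 35 patients are too few to split the endpoint by it.
5. Reconcile the Overview, 5.1 and 7.1.3 on the handling of non-urgent findings, and 7.3.2 and 7.6 with endpoint 4 on pacemaker and ICD implantation.

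The cost is about five CRF fields (prompted or not, episode date, anticoagulant start, reported or not, date reported) and revised endpoint wording. Attribution is a judgement made in an open-label study, so some subjectivity enters. The ILR-prompted rate will probably be lower than the undivided proportion.
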